## Abstract

**Purpose:**

To develop a study protocol for determining the optimal timing of Transcutaneous Electrical Acupoint Stimulation (TEAS) to enhance postoperative recovery in elderly patients. The study aims to evaluate different timing strategies for TEAS administration and their effects on postoperative outcomes, with the goal of improving clinical practices and guiding future research.

**Methods:**

A total of 266 geriatric patients who underwent radical resection of gastrointestinal tumors will be divided into seven groups: one control group (receiving standardized perioperative management), one sham intervention group (receiving TEAS treatment without electrical stimulation), and five intervention groups (receiving TEAS at different time intervals). The intervention groups will receive TEAS at bilateral Neiguan (PC6) and Zusanli (ST36) acupoints. The TEAS treatment will employ an altered frequency of 2/100 Hz with disperse-dense waveforms and an adjustable intensity, ensuring the stimulation remains below 10 mA and within a tolerable range for the patient. The device will output an asymmetrical biphasic pulse wave, with a pulse width of 0.2 ms ± 30%, based on electromagnetic compatibility basic performance testing. The primary outcome will assess changes in cognition, measured using neuropsychological tests administered preoperatively and 3 days postoperatively, as well as the Telephone Interview for Cognitive Status-Modified (TICS-m) at 1, 3, and 6 months postoperatively. Secondary outcomes will include preoperative and 3-day postoperative measurements of interleukin-6 (IL-6), S100 calcium-binding protein β (S100β), tumor necrosis factor alpha (TNF-*α*), insulin-like growth factor 1 (IGF-1), and C-reactive protein (CRP). Additional data will be collected on the time to postoperative exhaust, defecation, eating, and the first postoperative ambulation. Numeric Rating Scale (NRS) scores will be recorded before and on the third day after the operation, alongside Activities of Daily Living (ADL) and Braden scale scores, which will be assessed before the operation and at the time of discharge.

**Discussion:**

This protocol aims to determine the optimal timing of TEAS for improving postoperative recovery in geriatric patients with gastrointestinal tumor.

**Clinical trial registration:**

ClinicalTrials.gov, identifier NCT05482477.

## Introduction

Transcutaneous electrical acupoint stimulation (TEAS) is a novel therapy that involves applying low-frequency pulse currents to specific acupoints on the skin’s surface. This therapy combines the benefits of both acupuncture and transcutaneous electrical nerve stimulation (TENS) to achieve therapeutic outcomes (1). TEAS is non-invasive, easy to administer, and well-accepted by patients (2).

Postoperative cognitive dysfunction (POCD) is a common central nervous system complication in cancer patients, with an incidence ranging from 8.9 to 46.1% (3). It primarily manifests as memory impairment, decreased information processing capacity, and declines or disruptions in attention, perception, abstract thinking, executive function, language, and motor skills (4, 5). POCD can be challenging to diagnose but may persist for months or even become a permanent condition (6), significantly impacting patients’ postoperative recovery, reducing their quality of life, increasing mortality rates, and burdening both family and medical social resources, thereby contributing to the overall economic and social burden (7, 8).

Studies have demonstrated that TEAS treatment administered 10–30 min before entering the operating room or continuously throughout the surgical procedure can reduce the incidence of POCD in elderly patients (9–12). TEAS administered either preoperatively or in combination with postoperative treatment has been shown to significantly improve postoperative cognition (13). Our research has demonstrated that perioperative TEAS can effectively reduce the postoperative inflammatory response and lower the incidence of POCD in geriatric patients (14).

Furthermore, studies have indicated that TEAS can alleviate postoperative pain in patients (15), reduce the time to the first flatus and defecation (16), and expedite post-surgical ambulation (17). In our previous study, we observed a significant difference in the Braden scale scores between the pre- and postoperative TEAS groups and the control group at the time of discharge, while the Activities of Daily Living (ADL) scores remained similar (18).

TEAS treatments administered at various times have demonstrated improvements in postoperative cognition. However, it is important to note that long-term electroacupuncture treatment may lead to the development of a ‘tolerance effect,’ which triggers a negative feedback mechanism and reduces the number of receptors, potentially diminishing its therapeutic efficacy (19). Therefore, this study aims to outline the protocol for a research project currently in the planning stage, designed to determine the optimal timing of TEAS for enhancing postoperative recovery in elderly patients.

## Methods and analysis

### Design

From January to December 2025, we will conduct a prospective, single-center, single-blind, randomized controlled trial at Northern Jiangsu People’s Hospital. Figure 1 illustrates the study flowchart.

**Figure 1 fig1:**
[figure not shown]
Flow chart of the study protocol. TEAS, transcutaneous electrical acupoint stimulation; TICS-m, Telephone Interview for Cognitive Status-Modified; IL-6, Interleukin-6; S100β, S100 calcium protein β; IGF-1, Insulin-like growth factor-1; TNF-α, tumor necrosis factor, CRP, C-reactive protein; NRS, numeric rating scale; ADL, Activities of Daily Living.

### Patient population and setting

The equation for sample size calculation, *n* = (Z*
_α/2_
* + Z*
_β_
*)^2^ × 2*σ*^2^/δ^2^ where σ represents the average score of the Mini-Mental State Examination (MMSE) evaluated on the third day after the operation between the two groups. Based on previous pre-experimental data, this study employs a two-sided test with *α* = 0.05 and a test efficiency of (1-β) = 0.9, resulting in Z_α/2_ = 1.96, Z_β_ = 1.282. *σ* denotes the standard deviation, while *δ* represents the mean difference of MMSE scores on the third day after the operation between the intervention and control groups. According to the pre-experiment results, σ is 2.35, δ is 2.0, and considering a 30% increase in the sample size, each group requires 38 patients. Therefore, a total of 266 patients will be sequentially enrolled after meeting the eligibility criteria, with the attending doctor informing each patient and obtaining their informed consent. This study adheres to the principles of the Declaration of Helsinki.

To expand our pool of research subjects, we will promote recruitment on the hospital’s official account. Throughout the intervention, patients will retain the final decision-making authority regarding their participation in the trial.

### Eligibility criteria

Inclusion criteria:Patients aged 60 years or older.Patients diagnosed with gastrointestinal tumors who undergo radical resection under general anesthesia at Northern Jiangsu People’s Hospital.American Society of Anesthesiology (ASA) classification I ~ III.Preoperative Tilburg frailty scale score less than 5 points.Preoperative D-dimer within normal limits.Participants have completed a formal education program lasting more than 5 years (20).Patients who are willing and able to give informed consent and comply with the study protocol.

Exclusion criteria:Preoperative cognitive dysfunction or a history of cognitive dysfunction, dementia, or delirium.History of severe depression, schizophrenia, or other mental or neurological disorders, or those currently taking antipsychotic or antidepressant medications.Patients with severe hearing or visual impairment without the use of assistive devices.Patients with communication difficulties.Male patients with an average daily pure alcohol intake ≥61 g or female patients with an average daily intake ≥41 g (21).Patients who have undergone surgical treatment within the past 3 months or who have been hospitalized preoperatively for more than 3 months.Patients with severe heart, liver, or renal failure.Patients with hypoxemia (blood oxygen saturation < 94%) for more than 10 min during surgery.Patients admitted to the ICU postoperatively.Patients who withdraw or die due to noncooperation or unforeseen circumstances.Patients participating in other clinical studies that may interfere with the results of this study.Patients who undergo emergency surgery.Patients with a history of acupuncture treatment.

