### Randomization and blinding

This is a single-blind study. To ensure random allocation, serial numbers from 1 to 266 will be placed in sealed opaque envelopes for the patients. Specifically, numbers 1–38 will correspond to the preoperative TEAS group, numbers 39–76 will be assigned to the intraoperative TEAS group, numbers 77–114 will belong to the postoperative TEAS group, numbers 115–152 will be designated for the pre- and postoperative TEAS group, numbers 153–190 will be allocated to the perioperative TEAS group, numbers 191–228 will be assigned to the sham TEAS group, and numbers 229–266 will be assigned to the control group. The randomization process will be conducted by a study administrator who is not directly involved in the study.

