**Figure 2 fig2:**
[figure not shown]
Location of acupoints.

The timing of TEAS treatments for each group were as follows:Preoperative TEAS group: 30 min before anesthesia (28).Intraoperative TEAS group: From 30 min before anesthesia to the end of surgery (29).Postoperative TEAS group: For 7 consecutive days after the operation, once daily in the morning, with each session lasting 30 min (30).Pre-and postoperative TEAS group: From 1 day before the operation until 7 days after, once daily in the morning, with each session lasting 30 min (30).Perioperative TEAS group: 30 min before anesthesia until the end of surgery, 1 day before the operation, and on the 1st, 2nd, and 3rd days after surgery in the morning, each session lasting 30 min (14).Sham TEAS group: Electrodes will be placed in the same manner as the perioperative TEAS group but without electrical stimulation. Participants will be informed that the treatment has no sensation.

Two nursing postgraduates, who will serve as interveners, are required to spend 2 months in the Traditional Chinese Medicine Department of the hospital, dedicating 4 h each day to learning the functions and locations of acupoints, as well as the inspection and use of the instruments. To be eligible to participate in this intervention, the interveners must successfully pass a final examination, which will assess both theoretical knowledge and practical skills, administered by the Traditional Chinese Medicine Department.

During the experiment, a specialist from the Chinese Medicine Department will be invited to assess the appropriateness of acupoint selection and treatment intensity on a weekly basis. If any inaccuracies are identified in either the acupoint selection or treatment intensity, the intervener will be required to rejoin the Traditional Chinese Medicine Department for further training until they can accurately locate the acupoints and determine the correct treatment intensity. If a patient is affected by any such inaccuracies, they will be required to withdraw from the study.

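### Any radical gastrointestinal resection is eligible, but allocation is unstratified and the stated analysis unadjusted: no bias, but lost precision in ranking five timings in arms of 38

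*Protocol article*

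**What the plan says.** **Population.** The Eligibility criteria section of the protocol article admits "Patients diagnosed with gastrointestinal tumors who undergo radical resection under general anesthesia" at one hospital. It sets no limit on tumour site, surgical approach or length of operation. It narrows the mix in other ways, for example "American Society of Anesthesiology (ASA) classification I ~ III", a Tilburg score below 5, no emergency surgery and no postoperative ICU admission.

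**Allocation.** According to the Abstract, patients "will be divided into seven groups". Under Randomization and blinding, "serial numbers from 1 to 266 will be placed in sealed opaque envelopes for the patients", and each arm owns one fixed run of 38 numbers, beginning with "numbers 1–38 will correspond to the preoperative TEAS group". No strata or blocks appear in this scheme.

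**Analysis.** The Statistical analysis section names ANOVA, Kruskal-Wallis, chi-squared and Fisher's exact tests. It names no covariate.

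**Exposure.** In the Intervention section, the intraoperative arm is stimulated "From 30 min before anesthesia to the end of surgery", and the perioperative arm has the same open-ended intraoperative part. Postoperative sessions last a fixed 30 minutes.

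**The concern.** The aim is to identify the best of five timings, partly on recovery outcomes: time to flatus, defecation, eating and ambulation, day-3 pain and CRP. It is plausible, though the article gives no figures, that these depend on which operation was done. Several small arms will differ in case mix by chance, and an arm with easier operations can move up the ranking for that reason. Variation due to the operation also stays in the error term of every unadjusted test.

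A second, separate point is that operation length determines stimulation time in two active arms. The article gives a possible tolerance effect of prolonged stimulation as part of its rationale, so the duration actually delivered matters for interpretation.

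**Working it through.** **1. The plan's own figure.** Inputs from Patient population and setting: "this study employs a two-sided test with *α* = 0.05", "a test efficiency of (1-β) = 0.9", SD 2.35, difference 2.0 MMSE points on day 3, plus 30%.

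n = (1.96 + 1.282)² × 2 × 2.35² / 2.0² = 29.02; 29.02 × 1.3 = 37.7, rounded up to 38; 38 × 7 = 266. The figure reproduces.

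**2. Assumptions.** The article gives neither the share of any operation type nor its effect on MMSE. I assume a share p of 30–50% and an effect D of 1, 2 or 3 MMSE points.

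**3. Chance imbalance.** The standard error of the difference in share between two arms is √(2p(1−p)/38). The other rows come from 400,000 binomial draws of seven arms of 38.

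| | p = 30% | p = 50% |
|---|---|---|
| SE, two given arms | 10.5 points | 11.5 points |
| Chance of ≥20 points, two given arms | 6% | 8% |
| Mean highest-minus-lowest gap, seven arms | 20 points | 22 points |
| Chance that this gap is ≥20 points | 49% | 60% |

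**4. Effect on MMSE.** A 20-point gap shifts a mean difference by 0.20 × D, which is 0.2, 0.4 or 0.6 points. The planned difference of 2.0 is for intervention versus control; no timing-versus-timing difference is stated.

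**5. Error rate.** These are null simulations with p = 50% and 20,000 trials per value of D. Over all randomisations, the unadjusted ANOVA rejects in 5.0–5.3% for D = 0 to 3, and the adjusted analysis in 4.8–5.2%. Only among trials where two given arms differ by 20 points or more does the error of that pair's unadjusted t-test rise, to about 7%, 12% and 16% for D = 1, 2, 3.

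**6. Precision gained by adjusting**, if 2.35 is the SD over all operations and p = 50%:
- Residual SD = √(2.35² − 0.25D²) = 2.30, 2.13, 1.81 for D = 1, 2, 3.
- Required n per arm, with the plan's 30%: 37, 31, 23 instead of 38.
- The expected range of seven arm means with no true difference is about 2.70 × SD/√38. It is 1.03 points at SD 2.35 and falls to 1.01, 0.93, 0.79 with the residual SDs. This is the noise in which the ranking is made.

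**7. Power, if 2.35 is instead the SD within one operation type.** The total SD is √(2.35² + 0.25D²) = 2.40, 2.55, 2.79. Power at 38 per arm falls from 96% to 95%, 93%, 88%. At 29 per arm it falls from 90% to 89%, 85%, 78%.

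**8. Stratifying without adjusting.** With the operation mix exactly balanced (6,000 trials per value of D), the unadjusted ANOVA rejects in only 3.8%, 2.1% and 0.6% for D = 1, 2, 3. The adjusted analysis stays at 4.3–5.2%. Stratification therefore has to be carried into the analysis.

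**The case against.** A reader might infer that chance differences in operation type will pass for a timing effect. The documents do not support that. Random allocation balances operation type in expectation, the 5% test already allows for departures from balance, and step 5 confirms it. The raised error rates apply only to trials in which a large imbalance has occurred.

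The 20–22 points is also a maximum minus a minimum, and the arms that are extreme on case mix need not be extreme on outcome. Take time to defecation, with an assumed within-type SD of 1 day and an assumed operation effect of 1 day at a 50% share. The expected range of seven null means rises from 2.70 × 1/√38 = 0.44 day to 2.70 × √1.25/√38 = 0.49 day, an increase of only 0.05 day.

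The article does not say how strongly the operation affects recovery, never mentions surgical approach, and narrows the case mix through its other criteria. Unstratified allocation is a legitimate design. All of this stands, and it limits the point to one of efficiency.

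Covariates may be named in an analysis plan that is not shown, so their absence from the article is not an error. The allocation point does not depend on that plan, because the article prints the whole map from number to arm and the map has no place for strata.

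Finally, stratifying cannot remove the link between operation length and stimulation time. That link follows from how the two arms are defined and would remain under perfect balance.

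**Conclusion.** This is a cheap improvement, not an error in the plan. Under true randomisation the stated design gives unbiased comparisons and keeps the overall 5% error. What it gives up is precision: 38 per arm could be 37, 31 or 23 for the same power if the operation shifts MMSE by 1, 2 or 3 points at a 50% share. The ranking of timings is correspondingly noisier. A 20-point imbalance accounts for 0.2–0.6 MMSE points, well short of the planned 2.0, but the article states no smaller difference between timings against which to judge it.

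These sizes rest on assumed operation shares and effects. They also assume that numbered envelopes reach patients in random order; if the order were not random, that would be a different problem. The dependence of stimulation time on operation length in the intraoperative and perioperative arms holds as a separate point of interpretation.

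**What to change.** - Before allocation starts, have the study administrator generate a list stratified by planned operation site (upper versus lower tract). Use randomly varying block sizes that are multiples of seven.
- Include planned site and planned approach as factors when analysing cognition, recovery times, pain and CRP. Use a regression model, on transformed or ranked values where data are non-normal, in place of the unadjusted ANOVA or Kruskal-Wallis test, which cannot take these factors. Use the planned operation, so that the factors are fixed before treatment.
- Record stimulation minutes for each patient and report them by arm, so that the exposure delivered in the intraoperative and perioperative arms can be seen.

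The cost is a new list, one or two model terms, slightly uneven final arm sizes from incomplete blocks, and a little more analysis work. No extra patients are needed. Stratification is possible only before allocation begins; the model terms can be fixed later, provided this is done before outcomes are examined.

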### Statistical analysis

All data will be analyzed using IBM SPSS software version 24.0. Research data following a normal distribution and expressed as x̄± SD will be analyzed using analysis of variance (ANOVA). For non-normally distributed data expressed as median (interquartile range), the Kruskal-Wallis H test will be applied. Categorical variables, presented as frequency (f) and percentages (%), will be analyzed using the chi-squared test and Fisher’s exact test as appropriate. Multiple imputation methods will be employed to handle missing data.

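### Events that can only happen after allocation are written as exclusion criteria, and a forced-withdrawal rule cannot apply to control, so the compared arms need not be the randomised arms

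*Protocol article*

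**What the plan says.** The exclusion list in the Eligibility criteria section of the protocol article contains "Patients with hypoxemia (blood oxygen saturation < 94%) for more than 10 min during surgery" and "Patients admitted to the ICU postoperatively.Patients who withdraw or die due to noncooperation or unforeseen circumstances". The Patient population and setting section says that the 266 patients are enrolled in sequence once they meet the eligibility criteria.

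The Intervention section (text after Figure 2) has a specialist check acupoint selection and treatment intensity weekly. If an error is found, "If a patient is affected by any such inaccuracies, they will be required to withdraw from the study".

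The same section gives the treatment schedule. The preoperative and intraoperative arms start 30 min before anaesthesia. The pre- and postoperative arm and the perioperative arm have a session on the day before surgery. Sham electrodes follow the perioperative schedule without current. The postoperative arm starts after surgery, and control has no electrodes.

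On incomplete data, the Statistical analysis section says: "Multiple imputation methods will be employed to handle missing data".

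**The concern.** Exclusion criteria should be decidable before a patient is allocated. Intraoperative hypoxaemia, postoperative ICU admission, withdrawal and death are not. If they remove patients from the trial, the arms that are compared are subsets selected by what happened after allocation, and randomisation no longer guarantees that the subsets are alike.

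The removed patients are unlikely to be a random sample. The trial's aim is better postoperative recovery; ICU admission and death are failures of recovery, and hypoxaemic or ICU patients are plausibly among the poorest scorers on day 3. Withdrawal carries no time limit and telephone follow-up runs to 6 months. Read literally, a patient who withdraws in month 5 is excluded even though day-3 data exist.

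The inaccuracy rule adds an imbalance by design. Control cannot trigger it, sham can trigger only its acupoint part, and the active arms differ in how often they are exposed to it. That touches the trial's own question, which compares timings, and not only TEAS against control.

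**Working it through.** **1. Order of events.** The Randomization and blinding section does not say when envelopes are opened. Four of the five TEAS arms, and sham, need their assignment at or before 30 min before anaesthesia, and some need it the day before. Allocation must therefore precede surgery, and all the listed events are post-randomisation in every arm. In those four TEAS arms stimulation has also begun before surgery. In the postoperative arm hypoxaemia, and possibly ICU admission, come before the first session.

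**2. The planned size and what its margin protects.** Inputs from Patient population and setting: "this study employs a two-sided test with" α = 0.05, "and a test efficiency of (1-β) = 0.9", and "σ is 2.35, δ is 2.0".

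- n = 2 × (2.35 × (1.96 + 1.282) / 2.0)² = 29.02 per arm.
- 29.02 × 1.3 = 37.7, so 38, which agrees with "considering a 30% increase in the sample size, each group requires 38 patients"; 7 × 38 = 266.
- Pairwise power by the same normal approximation is Φ(2.0 / (2.35 × √(2/n)) − 1.96): 0.96 with 38 per arm, 0.90 with 29 and 0.87 with 26.

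The stated size reproduces. The margin protects power when patients are lost. It does nothing for comparability.

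**3. Exposure to the inaccuracy rule.** Counting from the schedule: preoperative 1 session, intraoperative 1, perioperative 5, postoperative 7, pre- and postoperative at least 8, control 0. Assume that 1–2% of sessions are judged inaccurate, independently (the article gives no rate). The chance of at least one is 1 − (1 − p)^k:

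- k = 1: 1% to 2%
- k = 5: 1 − 0.99⁵ = 5% to 1 − 0.98⁵ = 10%
- k = 8: 1 − 0.99⁸ = 8% to 1 − 0.98⁸ = 15%
- control: 0%

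These are counts over the whole course; fewer sessions fall before the day-3 tests.

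**4. Size of a possible bias.** If a fraction r of an arm is removed and those patients score d points below the ones retained, the retained mean exceeds the all-randomised mean by r × d. The shift in a difference between two arms is d × (r₁ − r₂). All rates and gaps here are assumptions.

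- d = 3, 15% versus 5%: 3 × 0.10 = 0.30 points, and 0.30 / 2.0 = 15% of the planned difference.
- d = 2 to 4, removal rates 5 to 10 percentage points apart: 2 × 0.05 = 0.1 to 4 × 0.10 = 0.4 points.
- Extreme case, where the lowest scorers are removed from a normal distribution with SD 2.35 and no true effect. The retained mean rises by 2.35 × φ(z_r)/(1 − r), where z_r is the r-quantile. The spurious difference is 0.20 for 5% versus 10%, 0.39 for 5% versus 15%, and 0.46 for 0% versus 10%, which is 10% to 23% of 2.0.
- Equal removal, equally selective: 0.

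**5. Imputation.** Withdrawn patients are a natural source of missing values. Imputation fills gaps for patients in the analysis; it cannot restore patients defined as excluded.

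**The case against.** Several stronger readings are tempting, and the article does not support them.

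- **TEAS versus control as per-protocol versus intention-to-treat.** A reader might infer this from the inaccuracy rule. It is wrong: the hypoxaemia, ICU, withdrawal and death exclusions apply to control too, so both sides are restricted sets. Only the inaccuracy rule is asymmetric, and its acupoint part reaches sham.
- **Every arm comparison is biased.** The most that can be said is that comparisons can be. Until its first session the postoperative arm is treated like control, so stimulation cannot make intraoperative hypoxaemia differ between those two.
- **All the events follow the start of stimulation.** That holds for four TEAS arms. What holds in every arm is that they follow allocation, and that timing is inferred from the schedule.
- **The imputation plan is contradicted.** It still has work to do for missed tests, assays and telephone calls among patients who stay in. There is only a tension over withdrawn patients.

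The sizes are also open to challenge. The 0.3-point illustration is below one standard error of a pairwise difference, 2.35 × √(2/38) = 0.54. Interveners train for 2 months, must pass an examination and are checked weekly, so high rates of inaccuracy should not be presumed.

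Finally, an article may leave the definition of the analysis set to a fuller document, and its absence is not held against the plan here. What remains is that the removal rules are stated explicitly, and nothing in the article brings the removed patients back.

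**Conclusion.** The concern holds. The article treats hypoxaemia during surgery, postoperative ICU admission, withdrawal and death as exclusion criteria although they can only arise after allocation, and it forces patients out for inaccurate stimulation under a rule that control cannot trigger. Followed as written, the plan compares selected subsets of the randomised arms.

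Selection bias is possible, of unknown size and direction. Under the assumed rates and score gaps above it would be roughly 0.1 to 0.46 MMSE points against the planned 2.0, and zero if removal is equal and equally selective. None of these rates comes from the article. The conclusion rests on allocation preceding surgery, which the schedule requires, and on the exclusions being applied as worded. It should be settled before recruitment, because outcomes not collected after removal cannot be recovered.

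**What to change.** - Limit the eligibility criteria to facts known before allocation.
- Record hypoxaemia, ICU admission, withdrawal and death by arm as post-randomisation events.
- Replace the required study withdrawal for inaccurate stimulation with a recorded protocol deviation, keeping the patient's data and follow-up. Whether stimulation continues is a clinical matter and is not addressed here.
- Analyse all randomised patients in their assigned arm. Any restriction to those who undergo the planned surgery is itself a post-randomisation restriction, so apply it identically in all arms and report the numbers by arm.
- Impute missing data for withdrawn patients; report deaths by arm rather than imputing them.
- Use the recorded deviations only in a per-protocol sensitivity analysis.
- Add a sensitivity analysis for data not missing at random, because some ICU patients may be untestable on day 3 for reasons tied to their condition.

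The cost is protocol wording and modest extra follow-up of patients already enrolled. The estimated effect may be somewhat diluted. The sample size stays at 38 per arm and 266 in total.
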